### Assignment of interventions: blinding

#### Who will be blinded {17a}

The researchers conducting the assessments will be masked when obtaining and analyzing ophthalmic examination data, which includes BCVA, IOP, OCT, and OCTA images. Data analysts will also be masked to ensure precise statistical results.

#### Procedure for unblinding if needed {17b}

This is an open-label trial, with no blinding for participants and surgeons.

### Data collection and management

#### Plans for assessment and collection of outcomes {18a}

Investigators will timely record the postoperative data after every visit. Two delegated investigators will be responsible for the data monitoring and will check the accuracy of the data every quarter. In cases where two assessors disagreed, a senior physician will be consulted for an additional evaluation.

### BCVA

After refractive error correction and optometric evaluation, BCVA will be tested using ETDRS chart (Precision Vision, Villa Prak, Illinois, USA). The logMAR values for finger counting, hand movement, light perception, and no light perception are 1.85, 2.3, 2.6, and 2.9, respectively [47]. An increase of ≥ 15 ETDRS letters, a change of < 15 ETDRS letters, and a decrease of ≥ 15 ETDRS letters is defined as “improving,” “invariant,” and “worsening” of visual acuity, respectively.

### Intraocular pressure

A non-contact computerized tonometer (CT-1, Topcon, Japan) will be used to measure the intraocular pressure (IOP). The average value obtained from three successive measurements will be noted. An intraocular pressure of at least 25 mmHg or a rise of at least 10 mmHg from the baseline is considered to be ocular hypertension.

### Slit lamp bio-microscopy

The eyes will be thoroughly examined with a 90D indirect ophthalmoscopy lens under a slit lamp.

### OCT

Three-dimensional spectral domain OCT (DRI-OCT Triton, Topcon, Inc, Tokyo, Japan) will be used to acquire all OCT scans. Scanning was centered on the macular fovea with a scan length of 6 mm. The resolution was 5 μm, the scan depth was 4 mm, and the scan mode was horizontal linear scanning of 512 × 128. CST refers to the average thickness of the distance between the retinal pigment epithelium (RPE) and the ILM at the highest point of the retina, which is measured at a circular area surrounding the foveal center with a diameter of 1 mm. Additionally, we will assess SRF, cystoid size (< 100 μm, 100–200 μm, > 200 μm) and location (outer nuclear layer (ONL) or inner nuclear layer (INL)), IS-OS continuity (completely continuous, partly disrupted, or completely disrupted), and presence and quantity of HRF (< 10, 11–20, > 20), vitreomacular interface (detached, vitreomacular adhesion, vitreomacular traction, and epiretinal membrane). The technicians will ensure that the images are centered and of sufficient quality. OCT images will be analyzed and compared preoperatively and at months 1, 3, 6, and 12.

### OCTA

OCTA images will be obtained following a standard protocol with the AngioVue OCTA system (RTVue-XR Avanti, Optovue, Fremont, California, USA). The scanning area, centered on the fovea, was captured in 3 × 3 mm sections with a resolution of 304 × 304 pixels. The in-built RTVue XR Avanti AngioVue software will help reveal FAZ, sVD, and dVD through the automated layer segmentation. Motion artifacts, a weak signal (5/10), poorly focused scans, or segmentation failure will all result in poor image quality, which will be disregarded. OCTA images will be analyzed and compared preoperatively and at months 3, 6, and 12.

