### Eligibility criteria {10}

The following are the criteria for the inclusion of candidates: (1) ≥ 18 years of age; (2) patients and their families fully understand the research and must sign an informed consent form; (3) diagnosed with type 1 or 2 diabetes mellitus; (4) hemoglobin A1c (HbA1c) levels of < 10% within 3 months; (5) moderate or severe nonproliferative diabetic retinopathy (NPDR) and proliferative diabetic retinopathy (PDR) without vitreous/preretinal hemorrhage [33]; (6) clear media for adequate OCT and OCTA images; (7) treatment-naïve DME diagnosed clinically; (8) CST of > 300 μm; (9) Early Treatment Diabetic Retinopathy Study (ETDRS) BCVA between 24 and 73 letters on the day of randomization; (10) treatment within 12 months of DME diagnosis; (11) no contraindication of vitrectomy or conbercept intravitreal injection. Each participant will only have one eye examined. If both eyes are qualified, the researcher will decide which of the eyes will be included in this study.

Exclusion criteria include the following: (1) any previous DME treatment (i.e., anti-VEGF injections, intravitreal corticosteroid usage, or macular photocoagulation); (2) macular edema caused by other diseases (i.e., age-related macular degeneration, retinal vein occlusion); (3) any previous intraocular surgeries (cataract surgery performed at least three months before study entry will not be exclusionary); (4) vision loss caused by other ocular diseases (i.e., glaucoma, high myopia); (5) a follow-up duration of < 12 months; (6) severe dysfunction of the heart, liver, kidney, lung, or other organs.

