#### Secondary outcomes

The secondary outcomes include the changes in BCVA and CST from baseline to months 1, 3, and 6; assessment of SRF, location and size of cystoid change, continuity of the IS-OS layer, and presence and quantity of HRF in OCT at months 1, 3, 6, and 12; assessment of FAZ, superficial capillary density (sVD), and deep capillary density (dVD) in OCTA at months 3, 6, and 12; re-treatment and diabetic retinopathy (DR) development from baseline to month 12; cost-effectiveness analysis at month 12; and vision-related quality of life (VRQL) at months 6 and 12.

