### Statistical methods

#### Statistical methods for primary and secondary outcomes {20a}

Descriptive statistics will be used to summarize study results and demographic variables. Means and standard deviations will be used to describe the normally distributed data, and medians and interquartile ranges will be used for non-normally distributed data. Categorical variables will be described as percentage and frequency. The two-sample *t*-test or Kruskal–Wallis test will be used to assess continuous variables, while the chi-square test will be used to evaluate categorical variables. A two-sided *p* value of less than 0.05 will be considered statistical significance. Besides, the records of patients with missing data will be deleted to ensure the accuracy of the results. All the data will be analyzed by SPSS 25.0 (Chicago, IL, USA).

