### Methods in analysis to handle protocol non-adherence and any statistical methods to handle missing data {20c}

Missing data will be managed using a combination of the last observation carried forward (LOCF) and multiple imputation (MI) methods. Sensitivity analyses will also be performed to assess the impact of different imputation methods on study results.

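### Discarding OCTA images after failed automated segmentation risks outcome-dependent missingness in FAZ, sVD and dVD, and the two missing-data rules conflict on what follows

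*Protocol article*

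**What the plan says.** - **Derivation.** Protocol article, OCTA: "The in-built RTVue XR Avanti AngioVue software will help reveal FAZ, sVD, and dVD through the automated layer segmentation".
- **Rejection.** Same section: "Motion artifacts, a weak signal (5/10), poorly focused scans, or segmentation failure will all result in poor image quality, which will be disregarded". The section mentions neither correction of the layer boundaries nor a repeat scan before an image is rejected.
- **Role.** Secondary outcomes: "assessment of FAZ, superficial capillary density (sVD), and deep capillary density (dVD) in OCTA at months 3, 6, and 12".
- **Population.** Eligibility criteria {10} require "8) CST of > 300 μm" and media clear enough for imaging at entry. The OCT section plans to grade cysts (up to the class above 200 μm), subretinal fluid and disruption of the IS-OS layer, so distorted layers are expected.
- **Missing data, rule A.** Statistical methods {20a}: "the records of patients with missing data will be deleted to ensure the accuracy of the results".
- **Missing data, rule B.** Section {20c}: "Missing data will be managed using a combination of the last observation carried forward (LOCF) and multiple imputation (MI) methods", followed by "Sensitivity analyses will also be performed to assess the impact of different imputation methods on study results".
- **Masking.** Section {17a} masks the researchers who obtain and analyse the images, OCTA included.

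**The concern.** The rejection rule operates after randomisation, and one of its triggers, segmentation failure, may be linked to the state of the retina. It is a reasonable inference, though not a statement in the document, that software which finds layers will fail more often where cysts and fluid distort them. Reducing that distortion is what both treatments are meant to do. If so, the chance that an eye contributes an OCTA value depends on how well its treatment worked. The arm with more residual oedema loses more of its worst eyes, and the eyes compared are no longer the randomised groups.

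The entry requirement for clear media does not help here, since it concerns opacity at baseline rather than segmentation at follow-up. Masking prevents subjective rejection but not an algorithm that fails in worse eyes. The background section sets out to learn which biomarkers favour surgery over anti-VEGF treatment. That question would be answered mainly from eyes that responded.

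**Working it through.** **1. What the document quantifies.** For OCTA, nothing: it gives no discard rate, no association between oedema and failure, and no difference by arm. Its only sample-size calculation is for BCVA. The 46 per arm reproduces (margin 5, SD 9.5, one-sided α 0.05, t distribution: n = 46, power 0.805), but it has no bearing on this point. The CST figures under Sample size {14} (364 ± 88.6 and 200 ± 210 μm) are not labelled as level or change, so they cannot fix the arm difference in residual oedema. All inputs in steps 2 to 4 are therefore assumptions.

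**2. Two-class illustration.** Assume residual oedema in 30% versus 50% of eyes, dVD 5 points lower in oedematous eyes, and 40% of oedematous and 5% of dry images discarded.
- True difference: (0.50 − 0.30) × 5 = 1.0 point.
- Oedematous share among usable images, first arm: 0.30 × 0.60 / (0.30 × 0.60 + 0.70 × 0.95) = 0.180 / 0.845 = 0.213. Images lost: 15.5%.
- Second arm: 0.50 × 0.60 / (0.50 × 0.60 + 0.50 × 0.95) = 0.300 / 0.775 = 0.387. Images lost: 22.5%.
- Observed difference: (0.387 − 0.213) × 5 = 0.87 point, an attenuation of 13%.

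**3. Continuous illustration.** Simulation with 500,000 eyes per arm; oedema in SD units; arms 0.5 SD apart; 20% of control images discarded; discard probability logistic in oedema. Attenuation = 1 − observed / true.

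| Oedema–density correlation | Logistic slope per SD | Discarded, control / study | True (SD) | Observed (SD) | Attenuation |
|---|---|---|---|---|---|
| 0.3 | 0 | 20% / 20% | 0.149 | 0.149 | none |
| 0.3 | 1 | 20% / 14% | 0.148 | 0.135 | 9% |
| 0.3 | 2 | 20% / 11% | 0.153 | 0.123 | 20% |
| 0.5 | 0 | 20% / 20% | 0.251 | 0.250 | none |
| 0.5 | 1 | 20% / 14% | 0.248 | 0.224 | 10% |
| 0.5 | 2 | 20% / 11% | 0.256 | 0.204 | 20% |

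With equal residual oedema in the arms, or zero correlation, true and observed differences all lie within 0.005 of zero. So bias needs all three conditions: discarding depends on oedema, oedema relates to the measure, and the arms differ in oedema.

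**4. Loss of precision.** If 30% of baseline and 15% of follow-up images were lost independently, 51 × 0.70 × 0.85 = 30.3, so about 30 of 51 eyes per arm would keep a baseline and follow-up pair. This shows lost information, not selection, because it assumes equal and independent loss.

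**5. The two missing-data rules side by side.**
- Deletion ({20a}) leaves the selection of steps 2 and 3 in place.
- Carrying forward ({20c}) gives a failed month-12 scan a value from an earlier visit, when oedema may have been different.
- Multiple imputation ({20c}) helps to the extent that its predictors explain the failure. A suitable one exists: Table 1 schedules OCT at every OCTA visit, and the OCT section shows that CST comes from a different device.

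The document does not say which rule governs a discarded OCTA image.

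**The case against.** The strongest reply has four parts.

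- **Rejecting failed segmentations is ordinary quality control.** Keeping them would add invalid measurements. This stands: the point is not that unreadable images should be kept.
- **An article condenses the full protocol.** The images follow a standard protocol that may include repeat scans or boundary correction, and discard tables usually belong elsewhere. This stands in part: the missing detail alone would be no finding. But the article does fix a rule, that failed segmentation means the image is disregarded, and gives two incompatible rules for the resulting gap.
- **The mechanism is not in the document.** This stands. A reader might infer that the most oedematous eyes will drop out according to treatment result and that a true difference will shrink. The text does not support that as fact. Further intervention also makes as-needed conbercept available to both arms, so a difference in residual oedema is not assured. Nor is it clear which arm would lose more images to cataract: lens surgery can accompany vitrectomy in the study group, but later cataract surgery is allowed without restriction by arm.
- **Section {20c} may keep the eyes in.** This stands as far as it goes, but {20a} says the opposite, and imputation need not remove bias if failure depends on unobserved values.

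A second tempting inference is that {20a}, read literally, deletes a patient's whole record over one rejected image. With an assumed 10% independent loss, 51 × 0.9⁴ ≈ 33 per arm would keep all four OCTA visits, against the 46 required for BCVA. The document does not say that a rejected OCTA image removes a patient from the BCVA or CST analysis, and {20c} points the other way.

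**Conclusion.** The concern holds as a risk, not as a demonstrated bias. The plan discards images with failed segmentation after randomisation, states no correction step, and applies this to eyes in which layer distortion is expected. Availability of FAZ, sVD and dVD can therefore depend on residual oedema, and the arm comparison may be selected or attenuated. When the three conditions hold together, the attenuation is roughly 9% to 20% in the simulated cases (13% in the two-class example), all on assumed inputs; if any one fails, it is nil. The conflict between {20a} and {20c} is plain in the text and makes matters worse, because the deletion rule would leave any selection uncorrected. The effect is confined to secondary outcomes; BCVA and CST are not affected by the discard rule itself.

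**What to change.** 1. In the OCTA section, have the masked image analysts attempt manual correction of the segmentation boundaries before an image is discarded. Discard only images that remain unreadable.
2. For OCTA outcomes, replace the record deletion in {20a} with the multiple imputation in {20c}, with same-visit CST as a predictor. Do not use LOCF for failed scans.
3. Report discarded images by arm, visit and reason.

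The cost is some reading time, one table and some added reader variation from manual correction. The readers are already masked and CST is already measured at every OCTA visit, so no new assessment is needed. Trial status says recruitment has not begun, so the rule can be set before any data exist.

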### DR classification

DR will be graded and classified according to International Clinical Diabetic Retinopathy and Diabetic Macular Edema Disease Severity Scales [33].

### Cost-effectiveness analysis

Clinical efficacy will be assessed based on BCVA and CST at the last follow-up and compared to that before operation. Cured: BCVA increased ≥ 15 ETDRS letters, CST decreased ≥ 20%, and no cystoid change is observed; improved: BCVA increased ≥ 5 ETDRS letters, CST decreased ≥ 10%, and no cystoid change is observed; invalid: BCVA and CST have no obvious change or deterioration. Effective rate = [*n* (cured) + *n* (improved)]/*n* (total). Costs include direct, indirect, and hidden costs. The registration fees and related examination fees are considered the same, and indirect or hidden costs such as transportation fees and late work fees are ignored. The treatment and drug costs are included in the direct medical cost, which is calculated according to the treatment and drug charge standard in 2023 of Tianjin Third-Level First-Class Hospital. The incremental cost-effectiveness ratio (ICER) is used as the evaluation index in cost-effectiveness analysis. Cost-effectiveness ratio = treatment cost/effective rate. ICER is the ratio of the difference between the treatment costs of the two groups and the difference between the effective rate of the two groups, indicating the cost of each additional effective patient in the study group versus the control group. The average cost of the two groups of treatments is taken as the willingness to pay. If ICER is less than the willingness to pay, the treatment scheme is cost-effective.

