### Further intervention

Thereafter, each participant will receive pro re nata (PRN) conbercept therapy, with regular monitoring for 12 months, at least 1 month apart for the vitrectomy of the study group and 3 months apart for the first intravitreal injection of the control group. PRN conbercept treatment will be performed if the following criteria are met: (1) existence of recent or persisting cystoid retinal lesions, (2) a decrease of no less than 5 ETDRS letters in BCVA, and (3) an increase of 50 μm or more in CST compared with the best value previously achieved. If high-risk PDR without definite vitreous or preretinal hemorrhage or severe NPDR with high-risk characteristics and reduced visual acuity are present, PRP treatment will be administered. Cataract surgery will also be allowed for cataract that affect vision. PPV will be performed if there exist un-clearing vitreous hemorrhage (1–6 months) and/or tractional retinal detachment. Patients with postoperative ocular hypertension will first receive drug treatment to lower their intraocular pressure. If medication is unable to control persistent high intraocular pressure, they will undergo anti-glaucoma surgery. Other further interventions will be conducted based on the specific circumstances.

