	**Study period**										
	**Enrollment**	**Allocation**	**Post-allocation**								**Close-out**
**Time point**	***T***_**1**_	**0**	***T***_**0**_	***T***^*****^_**1(1d)**_	***T***^*****^_**2(1w)**_	***T***_**3(1 m)**_	***T***^******^_**4(2 m)**_	***T***_**5(3 m)**_	***T***_**6(6 m)**_	***T***_**7(12 m)**_	***T***_**x**_
Enrollment:											
Eligibility screen	X										
Informed consent	X										
Allocation		X									
Interventions:											
PPV			X								
IVC			X			X	X				
Assessments:											
Demographics data	X										
Medical history	X										
Laboratory examination	X										
Eye examination	X			X	X	X	X	X	X	X	
BCVA	X					X		X	X	X	
IOP	X			X	X	X	X	X	X	X	
OCT	X					X		X	X	X	
OCTA	X							X	X	X	
Direct medical cost										X	
NEI-VFQ-25	X								X	X	
Adverse events			X	X	X	X	X	X	X	X	

*PPV*, pars plana vitrectomy; *IVC*, conbercept intravitreal injection; *BCVA*, best corrected visual acuity; *IOP*, intraocular pressure; *OCT*, optical coherence tomography; *OCTA*, OCT angiography; *d*, day; *w*, week; *m*, month

^*^Only study group

^**^Only control group

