## Discussion

The high incidence of refractory persistent DME necessitates the research for a more efficacious method for treating DME. Based on previous studies [30, 34–36], we have ample reasons to postulate that PPV is safe and effective for treatment-naïve DME. Moreover, PRP and cataract surgery can be performed simultaneously with PPV, obviating the need for continual hospital visits for treatment. However, PPV has mostly been used to treat refractory DME before, and the long-term course of disease and repeated intravitreal injections may have caused irreversible damage to the retina. Hence, we are going to explore whether early PPV combined with ILM peeling can reduce the therapeutic burden of DME patients, prevent vision loss, and maintain long-term stabilization of diabetic retinopathy, thus becoming as an initial therapy choice for treatment-naïve DME patients. Furthermore, with the assistance of OCT and OCTA, we will assess the imaging biomarkers connected with surgical treatment effectiveness.

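### Registration and examination fees are set equal between groups, but scheduled visits differ by one and re-treatment visits may differ further, so the ICER omits a cost difference of unknown sign

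*Protocol article*

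**What the plan says.** The Cost-effectiveness analysis section opens its cost definition with "Costs include direct, indirect, and hidden costs". It then narrows the scope: "The registration fees and related examination fees are considered the same, and indirect or hidden costs such as transportation fees and late work fees are" left out. What remains is stated next: "The treatment and drug costs are included in the direct medical cost", valued at a 2023 hospital charge standard. The incremental measure follows: "ICER is the ratio of the difference between the treatment costs of the two groups and the difference between the effective rate of the two" arms. The same section also defines a cost-effectiveness ratio for each group (treatment cost over effective rate) and takes the average cost of the two groups as the willingness to pay.

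The visit schedule is in Table 1 (Participant timeline). The day 1 and week 1 visits are footnoted "Only study group" and the month 2 visit "Only control group". All three carry an eye examination and an IOP measurement.

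On re-treatment, the Further intervention section says that "each participant will receive pro re nata (PRN) conbercept therapy, with regular monitoring for 12 months". The Outcomes section lists re-treatment to month 12 as a secondary outcome.

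**The concern.** A cost item may be left out of an incremental comparison when it is the same in both groups, because it then cancels. The plan invokes that reasoning for registration and examination fees, but its own schedule does not give the groups the same visits. Re-treatment, which can bring further visits, is among the outcomes the trial compares. Declaring the fees equal therefore fixes by assumption a quantity that the trial could observe.

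At stake is a named secondary outcome. The ICER, the two cost-effectiveness ratios and the willingness-to-pay figure that the ICER is judged against all depend on which costs are counted. The primary comparison of BCVA and CST is not affected.

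**Working it through.** The plan gives no fee, no cost and no ICER value, so there is no stated figure to reproduce. The check is a count from Table 1, followed by the algebra of the omitted term.

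**Step 1. Scheduled contacts (Table 1)**

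| Item | PPV group | Control group |
|---|---|---|
| Visits after T0 | day 1, week 1, months 1, 3, 6, 12 | months 1, 2, 3, 6, 12 |
| Eye examination and IOP after T0 | 6 | 5 |
| Contacts including T0 | 7 | 6 |
| BCVA after T0 | 4 | 4 |
| OCT after T0 | 4 | 4 |
| OCTA after T0 | 3 | 3 |

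The scheduled difference is 6 − 5 = 1 basic visit per patient, with the PPV group the costlier. Scheduled acuity testing and imaging do not differ.

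**Step 2. Re-treatment visits.** Table 1 has no visit between months 3 and 6 or between months 6 and 12, while PRN treatment with monitoring runs to month 12. The PRN criteria refer to cystoid lesions, BCVA and CST, so judging them calls for acuity testing and OCT. It is a reasonable inference that some PRN care takes place at unscheduled visits with chargeable examinations. The document does not say how many, or how they divide between the groups.

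**Step 3. Omitted term.** Let f be the registration plus examination fee per visit (not given), k the mean number of re-treatment visits per patient in the control group minus that in the PPV group (not given), and Δ the effective rate in the PPV group minus that in the control group (not given, taken as positive). The net visit difference, PPV minus control, is 1 − k, so

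omitted ICER term = (1 − k) × f / Δ.

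| k | Net visits | Δ = 0.05 | Δ = 0.10 | Δ = 0.20 |
|---|---|---|---|---|
| 0 | +1 | +20f | +10f | +5f |
| 1 | 0 | 0 | 0 | 0 |
| 2 | −1 | −20f | −10f | −5f |
| 4 | −3 | −60f | −30f | −15f |
| 6 | −5 | −100f | −50f | −25f |

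For example, at k = 4 and Δ = 0.10: (1 − 4) × f / 0.10 = −30f. A positive entry means that the rule reports too low an ICER and so favours PPV; a negative entry means the reverse. A negative k, with more re-treatment visits in the PPV group, would enlarge the positive term.

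A single f is a simplification. If a basic visit costs f₁ and a re-treatment visit with OCT costs f₂, the term is (f₁ − k × f₂) / Δ, and the sign changes at k = f₁ / f₂ instead of at k = 1.

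**Step 4. The other two outputs.** Fees that are equal between groups cancel only in a difference. They do not cancel in the cost-effectiveness ratio of each group or in the average cost used as willingness to pay. At a flat fee f, the scheduled visits after T0 alone would raise that average by (6f + 5f) / 2 = 5.5f. Leaving the fees out therefore also lowers the threshold that the ICER must meet.

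**The case against.** The strongest defence is that this is an openly declared simplification and nearly true for the scheduled part. If the examination fees in question are mainly acuity testing, OCT and OCTA, Table 1 schedules these identically. That stands. A reader might take 6 against 5 visits to mean 20% more examination cost in the PPV group, but the count is of basic visits, not of fees.

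Second, monitoring for 12 months is described for every participant, and some PRN injections may fall at scheduled visits. This also stands: extra re-treatment visits are an inference, and the article does not state that re-treatment is expected to differ.

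Third, a reader might infer that the ICER ignores re-treatment burden altogether. The document does not support that. Treatment and drug charges for PRN injections are counted, and re-treatment and NEI-VFQ-25 are assessed as outcomes in their own right.

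Fourth, the Discussion phrase "obviating the need for continual hospital visits for treatment" could be read as an expectation of fewer follow-up visits after PPV. In its sentence it refers to doing PRP and cataract surgery in the same session as PPV, so it is no evidence about PRN or follow-up visits.

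Fifth, the opening list of cost types could be read as contradicting what is computed. The next sentences narrow it explicitly and Table 1 lists only direct medical cost, so this is a matter of wording. A direct-cost perspective is a legitimate choice.

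These points limit the size of the concern but do not make the fees equal. The schedule differs by one visit, and the remaining difference can be counted from the trial's own records.

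**Conclusion.** The concern holds in a limited form. The equal-fee rule does not match the plan's own schedule and removes a cost difference from the ICER numerator. The certain part is small: one basic visit net, whose omission favours PPV. The re-treatment part could be larger and could run the other way. At a single fee per visit the two balance at k = 1, and beyond that the omission works against PPV. At an assumed 10-point difference in effective rate, each net visit is worth 10f in the ICER; at 5 points 20f, and at 20 points 5f.

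No currency amount follows, because the document gives no fees, effective rates or re-treatment counts. It is likewise not shown that the omission would change the cost-effectiveness conclusion, since the term cannot be set against the difference in treatment cost. What is lost is visit-related fees, not the cost of re-treatment. The change is worth making because it is cheap and replaces an assumption with a count.

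**What to change.** Replace the equal-fee assumption with wording such as: registration and examination fees are counted for each patient from the visits and examinations actually made, scheduled and PRN, valued at the same 2023 charge standard and added to treatment and drug cost. Use this total in the ICER, in the cost-effectiveness ratio of each group and in the average that sets the willingness to pay.

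Add one stated rule for visits shared with fellow-eye care, which the concomitant-care section permits, because a registration fee for such a visit cannot be assigned cleanly to the study eye.

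Optionally, describe the costs as direct medical costs, so that the definition matches what is computed and what Table 1 lists.

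The cost is slightly more data work: a count of visits and examinations per patient at a single site that already uses an electronic data capture system and collects direct medical cost at month 12, multiplied by fees from a tariff already chosen. No treatment, visit or clinical rule changes.

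### The cost-effectiveness rule sets no condition on the sign of the effect difference, so its verdict is reversed whenever vitrectomy is the less effective arm

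*Protocol article*

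**What the plan says.** All elements are in the protocol article, section Cost-effectiveness analysis.

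- **Effect.** The effective rate is the share of patients classed as cured or improved, a composite of BCVA gain, CST reduction and absence of cystoid change.
- **Cost.** "The treatment and drug costs are included in the direct medical cost". No amounts are given.
- **Ratio.** The arms are compared through this definition: "ICER is the ratio of the difference between the treatment costs of the two groups and the difference between the effective rate of the two" […]. It is read as "indicating the cost of each additional effective patient in the study group versus the control group", which fixes the direction as PPV minus conbercept.
- **Threshold.** "The average cost of the two groups of treatments is taken as the willingness to pay".
- **Decision.** "If ICER is less than the willingness to pay, the treatment scheme is cost-effective".

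Neither this section nor any other states what happens if PPV has the lower effective rate, if one arm dominates, or if the two rates are equal. The Secondary outcomes section lists cost-effectiveness at month 12.

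**The concern.** A ratio of two differences loses the sign of each. A negative value can mean cheaper and better, or dearer and worse. A positive value can mean paying more for a gain, or saving money at the price of a loss. Comparing the ratio with a threshold in one fixed direction is valid only when the effect difference is positive.

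The article states a complete decision rule, so following it literally could lead the trial to report PPV as cost-effective when it is both more expensive and less effective. Reducing the treatment burden, including its economic side, is part of the trial's rationale, so this conclusion would be read and used.

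The threshold raises a second, separate question. It is computed from the same costs that it is meant to judge.

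**Working it through.** The article gives no cost, effective rate, ratio or threshold value, so there is no stated figure to reproduce. The check applies the rule as written.

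**Definitions.** dC = cost(PPV) − cost(IVC). dE = effective rate(PPV) − effective rate(IVC). ICER = dC/dE. WTP = [cost(PPV) + cost(IVC)]/2, which is always positive. The written rule accepts PPV if ICER < WTP. The reference is incremental net benefit, NB = WTP × dE − dC, which accepts PPV if NB > 0.

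**Algebra.** NB > 0 means dC < WTP × dE.

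- If dE > 0, dividing by dE keeps the inequality: dC/dE < WTP. The written rule and net benefit agree, including when PPV is cheaper and better.
- If dE < 0, dividing by dE reverses it: NB > 0 requires dC/dE > WTP. The written rule then gives the opposite verdict.
- If dE < 0 and dC > 0, the ICER is negative and WTP positive, so the rule always accepts a dominated PPV.
- If dE = 0, the ICER is undefined.

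Only WTP > 0 is used, so the result does not depend on how the threshold is set.

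**Numerical illustration** (all costs and rates assumed, costs in arbitrary units):

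| Case | Cost PPV v IVC | Rate PPV v IVC | ICER | WTP | Written rule | NB |
|---|---|---|---|---|---|---|
| Dearer, less effective | 20 v 15 | 50% v 60% | 5/(−0.10) = −50 | 17.5 | accept | 17.5×(−0.10) − 5 = −6.75 |
| Cheaper, more effective | 15 v 20 | 60% v 50% | −5/0.10 = −50 | 17.5 | accept | 17.5×0.10 + 5 = +6.75 |
| Cheaper, much less effective | 13 v 15 | 40% v 60% | −2/(−0.20) = 10 | 14 | accept | 14×(−0.20) + 2 = −0.8 |
| Cheaper, slightly less effective | 0.8 v 1.0 | 55% v 60% | −0.2/(−0.05) = 4 | 0.9 | reject | 0.9×(−0.05) + 0.2 = +0.155 |
| Dearer, more effective | 1.2 v 1.0 | 80% v 50% | 0.2/0.30 = 0.667 | 1.1 | accept | 1.1×0.30 − 0.2 = +0.13 |

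The first two rows have the same ICER and the same WTP, so the rule cannot tell the worst case from the best. Rows three and four are reversed. Rows two and five are correct.

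**How easily dE < 0 can arise.** The Sample size section gives 46 evaluable and 51 randomised per arm. Assume a true effective rate of 60% in both arms. Exact binomial sums then give:

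- 46 per arm: PPV's observed rate is lower with probability 45.8% and tied with probability 8.5%.
- 51 per arm: 46.0% and 8.0%.

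With equal true rates from 30% to 60%, the chance of a lower observed rate stays between 45.5% and 46.1% at these two sizes, and the chance of a tie between 7.9% and 9.1%.

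**Threshold.** Since WTP = [cost(PPV) + cost(IVC)]/2, each unit added to PPV's cost raises the threshold by half a unit. With conbercept at 15, moving PPV from 20 to 30 moves the threshold from 17.5 to 22.5.

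**The case against.** The strongest defence is context. The article explains the ratio as "indicating the cost of each additional effective patient in the study group versus the control group", which presupposes that PPV produces additional effective patients. In that case the rule is correct, and one added sentence would repair it. This stands as a guide to what the authors probably had in mind. It does not restrict the rule, because it interprets the ratio and sets no condition on the verdict. Nor is this a detail left to an analysis plan, since the article states the rule in full.

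Several stronger readings are tempting, and the documents do not support them.

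- A reader might infer that the average-cost threshold causes the wrong verdicts. It does not: the reversal occurs with any positive threshold. The threshold is a separate weakness.
- A reader might infer that a non-inferiority design implies an effect difference near zero. The 5-letter margin applies to mean BCVA change, whereas the economic effect is a composite response rate for which the article gives no expected value.
- A reader might take the 46% and 8% as estimates for this trial. They describe equal true rates, which is an assumption.
- A reader might add that "The registration fees and related examination fees are considered the same" although Table 1 gives the arms slightly different visits. This is a declared simplification, no fees are given, and nothing shows that it matters beside surgery and drug costs. It is not part of this point.

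**Conclusion.** The rule is wrong as written. It lacks a condition on the sign of the effect difference. It therefore accepts every dominated PPV, reverses the verdict when PPV is cheaper and less effective, and has no answer when the rates tie. It is right whenever PPV is the more effective arm. This is algebra and rests only on a positive willingness to pay. The costs, rates and probabilities shown are illustrations under assumed values.

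As a lesser and separate matter, the threshold is not an independent value of one additional effective patient, because it moves with the price of the treatment under assessment.

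The effect is confined to a secondary outcome. The BCVA and CST conclusions are untouched. The correction should nevertheless be made before the analysis.

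**What to change.** Replace the decision sentence with a net-benefit rule: incremental net benefit = WTP × (difference in effective rate) − (difference in cost), PPV minus conbercept. Call PPV cost-effective only if this is above 0, and give it with an uncertainty interval. It remains defined when the rates tie.

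Report dominance when the cost and effect differences have opposite signs: dearer and less effective is dominated, cheaper and more effective is dominant.

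Fix the willingness to pay per additional effective patient before the analysis, independently of the observed arm costs, and show the result over a range of values.

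The cost is a change of analysis text and a small amount of programming, with no change for patients or visits. The real effort lies in choosing and justifying the range for the willingness to pay, because the documents supply no value for this composite response.
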